## Abstract

**Background:**

Otosclerosis is characterized by bony deposits in the otic capsule, resulting in stapes fixation and progressive hearing loss. It can be treated effectively by surgically removing (part of) the stapes and replacing it with a prosthesis. Increasingly, stapes surgery is performed as a day-case procedure. The major drive towards day-case surgery has been out of economic considerations. However, it is also increasingly an explicit patient request and leads to shorter waiting times for surgery, a reduced risk of infection and most likely positively influences the patient’s quality of life as a result of rapid discharge and rehabilitation. Even though stapes surgery seems well suited to a day-case approach, given the low complication rates and early recovery, evidence is scarce and of low quality.

**Methods and design:**

A single-center unblinded randomized controlled trial was designed to (primarily) investigate the effect of hearing outcomes of day-case stapes surgery compared to inpatient stapes surgery and (secondarily) investigate the effect of both methods on quality of life, tinnitus, vertigo and cost-effectiveness. One hundred and twelve adult otosclerosis patients who are eligible for stapes surgery will be randomly assigned to either the day-case or inpatient treatment group. The primary and secondary outcome measures will be assessed using pure-tone audiometry (at approximately 2 months and 1 year follow-up), questionnaires (at 3 months and 1 year follow-up) and costs diaries (weekly the first month after which once a month until 1 year follow-up).

**Discussion/conclusion:**

This trial allows for a comparison between day-case and inpatient stapes surgery to investigate the hypothesis that day-case stapes surgery is associated with a higher quality of life and higher cost-effectiveness, while maintaining equal hearing results, compared to inpatient stapes surgery.

**Trial registration:**

Netherlands Trial Register (www.trialregister.nl): NTR4133, registration date 21^st^ August 2013.

**Electronic supplementary material:**

The online version of this article (doi:10.1186/s12901-016-0024-6) contains supplementary material, which is available to authorized users.

## Background

Otosclerosis is characterized by abnormal sponge-like bone growth in the otic capsule, causing progressive hearing loss, vertigo and/or tinnitus [1]. It mainly affects the ossicular chain and can be treated surgically by removing (part of) the stapes and replacing it with a prosthesis; stapedotomy and stapedectomy respectively. Numerous surgeons have reported either equal hearing results when comparing stapedotomy and stapedectomy or better results with stapedotomy [2–6]. Although stapes surgery has proven to be a safe and effective treatment option for otosclerosis [7], permanent sensorineural hearing loss can occur and is the most dreaded complication of stapes surgery. The incidence of this complication following primary stapes surgery has been reported to be less than 1 % in large series [8, 9]. Other complications associated with stapes surgery are postoperative vertigo in 12-45 % of patients [10–13] and tinnitus in 8-54 % of patients [14–17].

Currently, in our clinic, stapes surgery involves overnight hospital stay. Many other otologic procedures that involved overnight hospital stay in the past are presently being performed on an outpatient basis successfully [18–20]. Ear, nose and throat (ENT) surgery is well suited to a day-case approach as many of the disease entities are benign and procedures are associated with low complication rates [18]. Even though one of the major drives towards day-case surgery has been financial, other non-financial benefits are of major importance. Day-case surgery is associated with shorter waiting time for surgery and reduced risk of infection [21]. Moreover, as a result of a more rapid social and emotional rehabilitation compared to overnight stay, patients might prefer day-case surgery.

Reports on day-case surgery for otosclerosis are scarce [22, 23]. One prospective case series of 24 consecutive otosclerosis patients undergoing day-case stapes surgery [22] reported a readmission rate of 12.5 percent, reasons being vertigo and asthenia. All of these patients were treated under general anesthesia. One prospective case-control study comparing ten day-case and ten inpatient stapedectomies [23] showed no difference in postoperative hearing thresholds, sensorineural hearing loss, speech audiometry or postoperative vertigo. All procedures were performed under local anesthesia. The authors did not report on quality of life (QoL) following day-case surgery.

The lack of (high-quality) studies precludes firm evidence-based recommendations and demonstrates the need for high-quality studies quantifying the benefits of day-case surgery, both clinical and financial. In order to accommodate this need, in this study we shall compare day-case stapes surgery to inpatient stapes surgery. The study will be conducted as a randomized controlled trial.

## Methods and design

This protocol is reported according to the SPIRIT Statement, an international guideline on reporting protocols [24].

### Study objectives

The primary objective of this study is to evaluate effectiveness of day-case stapes surgery compared to in-hospital stapes surgery followed by one-day hospital admittance for otosclerosis, in terms of hearing improvement. In addition, subjective participants’ perception on hearing improvement, QoL, tinnitus, vertigo and cost-effectiveness will be assessed.

### Study design

The study design will be a single-center, unblinded, randomized controlled trial. Subjects will be assigned to one of two groups: day-case surgery under general anesthesia or inpatient stapes surgery under general anesthesia followed by one-day hospital admittance (Fig. 1).

**Fig. 1 Fig1:**
[figure not shown]
Flow diagram of Day-case stapes surgery study. Abbreviations: RCT = Randomized Controlled Trial, TBQ = Tinnitus Burden Questionnaire, VBQ = Vertigo Burden Questionnaire

### Study population

The study population consists of adults with otosclerosis, as diagnosed in the outpatient clinic of the ENT department at the University Medical Center Utrecht (UMC Utrecht), the Netherlands, who will be undergoing (revision) stapedotomy. In order to be eligible to participate in this study, a subject must meet all of the following criteria:

#### Inclusion criteria

Age ≥ 18.Otosclerosis based on a clinical history of progressive hearing loss and pure-tone audiometry showing conductive hearing loss with an air-bone gap > 20 dB above normal adult hearing level and a perceptive hearing loss < 35 dB above normal adult hearing level in the range of 500, 1000, 2000 and 4000 Hz.Willingness and ability to participate in all scheduled procedures outlined in the research protocol.General health allowing general anesthesia in an outpatient setting as assessed by an anesthesiologist.Quick access to communication and transportation in case of any complications.Good understanding of the Dutch language.

A potential subject who meets any of the following criteria will be excluded from participation in this study:

#### Exclusion criteria

Previous middle ear surgery other than previous middle ear inspection or stapes surgery;Known aberrant (middle ear) anatomy in one or both ears based on a clinical history, otologic examination, imaging and/or previous middle ear inspection and assessed by an ENT surgeon;Co-morbid middle or inner ear pathology based on a clinical history, otologic examination, imaging and/or previous middle ear inspection and assessed by an ENT surgeon, including osteogenesis imperfect or an active ear infection in one or both ears;Disability that could interfere with audiologic evaluation and/or questionnaire fulfillment.

### Sample size calculation and recruitment

To establish equivalence in postoperative mean air conduction of 5 dB (standard deviation 10) between the day-case and the inpatient group with an alpha of 0.05 and a power of 80 %, 51 participants per group are needed. To anticipate on a withdrawal of 10 % of the participants, 5 more participants than needed will be recruited per group. At the ENT department in UMC Utrecht, we perform an average of 80 (revision) stapedotomies per year. Assuming a participation rate of 75 %, we will be able to include the necessary number of 112 patients in two years. If participants wish to leave the study or the investigator decides to withdraw a participant from the study for urgent medical reasons, these participants will not be replaced unless these account for more than 10 %.

Patients will be recruited from the outpatient ENT department of the UMC Utrecht. If an otosclerosis patient meets the criteria for stapes surgery and the inclusion criteria for this study, one of the researchers will explain the content of the study and provide the patient with written patient information and an informed consent form. Patients consent to the use of their data for the research purposes outlined in this protocol, which includes publication of the results once the trial has been completed. Further details can be found in Additional file 1 (informed consent form; translated to English, original in Dutch). Patients that do not want to be included in the study because they want to undergo stapes surgery in a clinical setting will be asked whether they want to fulfill the study procedures and whether their data can be used for analysis.

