### Statistical analysis

Baseline characteristics per group will be described as means and standard deviations. Differences in the baseline will be analyzed using the independent samples students *t-*test or non-parametric tests for continuous variables and the Fisher’s exact test for categorical variables.

The primary and secondary outcome data are quantitative and will be presented both continuous and categorical. Between-group mean differences, rate differences and rate ratios with 95 % confidence intervals will be calculated. For further analysis of between-group differences in both primary and secondary outcomes the independent samples students *t–*test or non-parametric tests will be used for continuous outcomes and the Fisher’s exact test for categorical outcomes. Within-subject comparisons will entail differences in mean values and percentages before and after stapes surgery. These will be analyzed using paired *t*-tests for continuous measures and the McNemar test for categorical outcomes.

Missing values will be handled using multiple imputation and all analyses will be performed on an intention-to-treat basis. A sensitivity analysis will be performed using all of the data acquired from patients that opted not to be included in the study, but did fill out the questionnaires and underwent pure-tone audiometric and speech audiometric follow-up.

The data will be reported according to the CONSORT Statement [37, 38].

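### The 51 per group said to give 80% power for equivalence within 5 dB is a one-sided sample size; equivalence power is about 61% at best

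*Protocol article*

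**What the plan says.** In the section on sample size calculation and recruitment, the protocol article gives the goal as "To establish equivalence in postoperative mean air conduction of 5 dB (standard deviation 10) between the day-case and the inpatient group". It sets alpha at 0.05 and power at 80%, and concludes that "51 participants per group are needed". For an expected 10% withdrawal, "5 more participants than needed will be recruited per group", which makes 56 per group and 112 in total. Withdrawals are not replaced unless they exceed 10%. The section does not state sidedness, a formula or an assumed true difference.

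The Abstract and the Discussion/conclusion describe the hearing aim as equal results in the two settings. Non-inferiority and one-sided testing are not mentioned anywhere. The section on statistical analysis plans interval estimates at the 95% level ("Between-group mean differences, rate differences and rate ratios with 95"), plus ordinary between-group t-tests or non-parametric tests. The interval is not tied to the 5 dB margin.

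**The concern.** An equivalence claim must exclude a difference of 5 dB or more in both directions, so the whole confidence interval has to fall between −5 and +5 dB. That takes more patients than excluding a difference in one direction. For a 5 dB margin and SD 10, 51 per group looks too small for a two-directional claim and close to what a one-directional claim needs.

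The stated power of the primary objective is at stake. If the two settings truly give identical hearing, the section implies a 2 in 10 chance of failing to show it. Should the real chance be much higher, an inconclusive result becomes likely and could be misread as evidence against day-case surgery.

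**Working it through.** **Inputs from the sample size section:** margin 5 dB, read as ±5 dB; SD 10 dB; alpha 0.05; power 80%; 51 completers per group; 56 recruited per group. Allocation is 1:1 (randomization section). **Assumption:** true difference 0 dB, which the article does not state. It is the value at which equivalence power is highest.

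**Step 1. Reproduce 51.** For one one-sided test, n per group = 2(SD/margin)²(z₁₋α + z₁₋β)², where 2 × (10/5)² = 8.

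- Normal approximation, one-sided 5%: 8 × (1.645 + 0.842)² = 49.5, so 50.
- Noncentral t, one-sided 5%: power is 79.9% at n = 50 and 80.6% at n = 51, so 51. This is the protocol's figure.

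**Step 2. Try the other readings.** For equivalence at true difference 0, the type II error is shared between two sides, so z for 80% power becomes z₀.₉₀ = 1.282.

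| Reading | Normal formula | n, normal | n, t-based |
|---|---|---|---|
| One-sided 5%, one direction | 8 × (1.645 + 0.842)² = 49.5 | 50 | **51** |
| Two-sided 5% difference test | 8 × (1.960 + 0.842)² = 62.8 | 63 | 64 |
| Equivalence, two one-sided 5% tests (90% CI) | 8 × (1.645 + 1.282)² = 68.5 | 69 | 70 |
| Equivalence, 95% CI within ±5 dB | 8 × (1.960 + 1.282)² = 84.1 | 85 | 86 |

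Only the first row gives 51.

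**Step 3. Equivalence power at 51 per group.** The standard error is 10 × √(2/51) = 1.980 dB, and 5/1.980 = 2.525. At true difference 0, power ≈ 2Φ(2.525 − z₁₋α) − 1.

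- Two one-sided 5% tests: 2Φ(0.880) − 1 = 62.1%. Integrating over the distribution of the estimated SD (t-based) gives **61.2%**.
- 95% CI within ±5 dB: 2Φ(0.565) − 1 = 42.8%. The t-based figure is **41.1%**.

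**Step 4. Sensitivity (t-based).**

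| Case | Two one-sided 5% tests | 95% CI rule |
|---|---|---|
| 51 per group, true difference 0 | 61.2% | 41.1% |
| 51 per group, true difference 1 dB | 55% | 37% |
| 51 per group, true difference 2 dB | 41% | 26% |
| 50 per group, true difference 0 | 59.8% | 39.4% |
| 56 per group (no withdrawal), true difference 0 | 67.5% | 49.2% |

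With 51 per group and true difference 0, 80% power would need a margin of about ±5.8 dB (two one-sided 5% tests) or ±6.5 dB (95% CI). Keeping ±5 dB, it would need an SD of about 8.6 or 7.7 dB. None of these values is stated.

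**Step 5. Withdrawal allowance.** 51/0.9 = 56.7, so 57 per group. 56 × 0.9 = 50.4, which is below 51. Five extra out of 56 cover 5/56 = 8.9%.

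**The case against.** - **The authors may have meant non-inferiority.** Then 51 is correct at one-sided 5% and the error lies in the word equivalence. This is plausible, but the text still has to change. Even then, if the planned 95% interval were used to judge non-inferiority, the test would be at one-sided 2.5%, and 51 per group would give 70.6% power.
- **No formula is shown, and the article condenses a fuller protocol.** That a one-sided test was used is inferred from the exact match. The inconsistency does not depend on the inference: the section states goal, inputs and result, and no standard equivalence calculation on those inputs gives 51.
- **The 41% is conditional.** This stands. The article plans 95% intervals in general terms and does not say they decide equivalence. The figure that rests on the stated alpha alone, read in the conventional way, is 61%.
- **The true difference of 0 is assumed.** It is, but any other value lowers the power.
- **The withdrawal shortfall is trivial.** Largely accepted. It is one patient per group, it moves power from 61.2% to 59.8%, withdrawals above 10% may be replaced, and multiple imputation is planned. It does not carry the finding.
- **Moving to non-inferiority is not just an edit.** This stands. It changes the primary hypothesis of a trial that is recruiting.

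**Conclusion.** The concern holds: the stated power is wrong as written. For equivalence within ±5 dB, with SD 10, 51 completers per group and a true difference of 0, power is 61.2% with two one-sided 5% tests, against the stated 80%. If the 95% interval is the decision rule, it is 41.1%. With truly identical settings, the chance of not showing equivalence is therefore about 39% or 59%, not 20%. The gap of 19 points or more is too large to come from rounding or the choice of approximation, and it remains even if nobody withdraws. Type I error is not affected; the consequence is a misstated power and a higher risk of an inconclusive primary result.

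**What to change.** Reconcile the stated aim with the 51 per group in the sample size section, before results are known. Two routes keep the enrolment as it is:

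1. **Keep equivalence and state its power.** Name the decision rule and give the power at true difference 0: 61% with two one-sided 5% tests (90% interval within ±5 dB), or 41% if the 95% interval must lie within ±5 dB. This costs wording and a less favourable stated power.
2. **Declare non-inferiority.** State a one-sided 5% test with a 5 dB margin, for which 51 per group gives 80% power at true difference 0. This changes the primary hypothesis, so it needs an amendment, matching edits to the Abstract and Discussion/conclusion, and an interval that fits one-sided 5%.

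The first route is the simpler correction because it leaves the declared aim untouched. In either case, say that five extra per group cover 8.9% withdrawal.

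If the primary analysis is to adjust for the preoperative threshold, give power as a function of the pre/post correlation ρ, using a residual SD of about 10√(1 − ρ²). At 51 per group, the SDs of 8.57 and 7.71 needed for 80% equivalence power correspond to ρ of about √(1 − 0.857²) = 0.52 (two one-sided 5% tests) or √(1 − 0.771²) = 0.64 (95% interval). The article gives no value for ρ, so this should be shown as a range.

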### Randomization, blinding and treatment allocation

A web-based randomization program (Julius Center, UMC Utrecht, Utrecht, The Netherlands) shall be used to allocate subjects randomly into two groups with stratification for age. Block randomization will be used with an allocation ratio of 1:1. The randomization chart, including block size, is established before the start of the study by an independent data manager and will not be available to any of the people involved with enrolment or treatment of participants. Consequently, treatment allocation sequence is concealed for participants, care providers and researchers. Blinding of both participants and care providers is not possible, since both participants and care providers will be aware of the surgical setting and hospital stay.

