### Intervention

The surgical procedures, as well as hospitalization in the inpatient group, will take place at the UMC Utrecht. Patients in both groups will undergo (revision) stapedotomy under general anesthesia. The surgical procedure will be performed by three surgeons according to standard protocol in the UMC Utrecht [7].

Patients allocated to the conventional group will be admitted one day before or the day of surgery and will be discharged one day after surgery. Patients allocated to the day-case group will be admitted into the outpatient unit one day before or on the day of the surgery and will be discharged the day of the surgery. Patients are not allowed to drive for 24 h following day-case surgery and will be recommended 24 h of relative bed rest. After a period of 24 h, patients can return to their daily routine. Participants will be asked to contact the hospital in case of severe postoperative vertigo or pain. The ear tampon will be removed in the outpatient clinic seven to ten days postoperatively in both groups.

It is to be expected that patients who have been operated on in day-case will sometimes stay overnight, for example due to postoperative nausea or dizziness. If patients are not physically capable of same-day discharge or if surgeons do not support this, patients will stay overnight. These patients will be asked to complete their follow-up and analyses will be carried out on an intention-to-treat basis.

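### Primary and revision stapedotomies are pooled, allocation is stratified for age only and the primary comparison is unadjusted, so surgical type costs precision that a prespecified model term would recover

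*Protocol article*

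**What the plan says.** The study population consists of adults with otosclerosis "who will be undergoing (revision) stapedotomy". The exclusion criteria rule out "Previous middle ear surgery other than previous middle ear inspection or stapes surgery", so an earlier stapes operation does not bar entry. Under Intervention the same mixture applies to both arms: "Patients in both groups will undergo (revision) stapedotomy under general anesthesia".

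Allocation will "allocate subjects randomly into two groups with stratification for age", and "Block randomization will be used with an allocation ratio of 1:1". No other stratification factor is named.

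The primary outcome is the postoperative air-conduction level at about two and twelve months, averaged over four frequencies. The sample size section plans the trial "To establish equivalence in postoperative mean air conduction of 5 dB (standard deviation 10) between the day-case and the inpatient group", with alpha 0.05, power 80% and 51 patients per group. It does not say whether the standard deviation of 10 dB describes the mixed population or one surgical type. The Statistical analysis section names the independent-samples t-test or a non-parametric test for continuous between-group comparisons, primary outcome included, and mentions no covariate.

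**The concern.** Whether an operation is a primary procedure or a revision is settled before the patient is randomised, because the eligibility check itself asks about earlier ear surgery. If the two types differ in expected postoperative hearing, surgical type is a baseline predictor of the primary outcome. The plan uses it neither in the allocation nor in the comparison.

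The outcome is a postoperative level and the test is unadjusted. Any excess of revisions in one arm therefore passes into the estimated difference in proportion to the hearing gap. In a trial that has to place a difference within 5 dB, avoidable noise widens the confidence interval and lowers the chance of showing equivalence. It also leaves an awkward result to explain if the arms turn out visibly unequal in revisions.

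**Working it through.** **Inputs from the protocol article.** Margin 5 dB, SD 10 dB, alpha 0.05, power 80%, 51 per group before the withdrawal allowance (Sample size calculation and recruitment); age as the only stratum (Randomization, blinding and treatment allocation); unadjusted test (Statistical analysis).

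**Assumed inputs, not in the article.** Share of revisions p = 10–30%; gap D in mean postoperative air conduction between revisions and primary operations = 5–10 dB.

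**The plan's own figure.** For one one-sided test at 0.05, n = 2 × 10² × (1.645 + 0.842)² / 5² = 49.5, so 50 per group. The version based on the t distribution gives 51, with power 0.806. The stated 51 therefore reproduces on a one-sided 0.05 basis, which is kept below. Whether that basis suits an equivalence claim is a separate matter.

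**Chance shift.** Treating the revision counts in the two arms as independent binomials:

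- SD of the difference in revision share = √(2p(1−p)/51) = 0.059, 0.079 and 0.091 for p = 10%, 20% and 30%.
- Shift in the air-conduction difference = imbalance × D; its 95% limit = 1.96 × SD × D.
- Share of the total variance due to surgical type = p(1−p)D²/100.

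| p | D (dB) | Mean absolute shift (dB; % of margin) | 95% limit (dB; % of margin) | P(shift ≥ 1 dB) | Variance share |
|---|---|---|---|---|---|
| 10% | 5 | 0.23 (5%) | 0.58 (12%) | 0.1% | 2.3% |
| 10% | 10 | 0.47 (9%) | 1.16 (23%) | 6.8% | 9.0% |
| 20% | 5 | 0.31 (6%) | 0.78 (16%) | 0.9% | 4.0% |
| 20% | 10 | 0.63 (13%) | 1.55 (31%) | 17.2% | 16.0% |
| 30% | 5 | 0.36 (7%) | 0.89 (18%) | 2.3% | 5.2% |
| 30% | 10 | 0.72 (14%) | 1.78 (36%) | 23.4% | 21.0% |

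For scale, the standard error of the difference from all sources is 10 × √(2/51) = 1.98 dB, so its 95% range is about ±3.9 dB. A shift of 2 dB or more from surgical type has probability 0.9% at p = 20%, D = 10 dB, and 2.3% at p = 30%, D = 10 dB.

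**Error rate.** In a simulation with simple randomisation, total SD 10 dB, a 90% confidence interval for equivalence and a true difference of 5 dB, the unadjusted comparison declared equivalence in 5.0% of trials at p = 20%, D = 10 dB. The rate was 4.9% in a more extreme case, p = 30%, D = 15 dB. It stays at its nominal level.

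**What adjustment gains, if 10 dB describes the mixture.** Residual SD = √(100 − p(1−p)D²):

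- p = 10%, D = 5 dB: √97.75 = 9.89 dB.
- p = 20%, D = 10 dB: √84 = 9.17 dB.
- p = 30%, D = 10 dB: √79 = 8.89 dB.

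On the one-sided basis the required number per group falls from 50 to 49, 42 and 40 respectively.

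**If 10 dB instead holds within a surgical type.** At p = 20%, D = 10 dB the total SD is √(100 + 16) = 10.77 dB. One-sided power of the unadjusted test at 51 per group then falls from about 81% to about 76%, and adjustment would recover it.

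**The case against.** The strongest reply is that randomisation makes this imbalance random. If the SD of 10 dB describes the mixture, variation due to surgical type is already in the standard error and in the 51 per group. That stands, and the simulation confirms it. A reader might infer that the estimate is biased, or that equivalence could be declared falsely more often; neither follows.

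A reader might also infer that imbalance could consume a large part of the 5 dB margin. The article does not support this: it gives neither p nor D. Even on the assumed values, 12–36% of the margin is a 95% limit, while the average is 5–14%. Both surgical types must meet the same limits on air-bone gap and perceptive loss, and aberrant anatomy is excluded for both, so the gap could be smaller than assumed.

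A third tempting reading is that low risk is being claimed for revisions on evidence from primary surgery, since the Background says "The incidence of this complication following primary stapes surgery has been reported to be less than 1 % in large series". That sentence is correctly labelled as concerning primary surgery, and the stated hypothesis contains no separate safety claim for revisions.

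Finally, a covariate or a breakdown by surgical type may sit in an analysis plan that is not shown. For the breakdown this is a full answer, and its absence from the article is no finding. For the comparison it is a partial answer: the article itself names an unadjusted test for the primary outcome, so this is a stated choice and not a silence. An analysis plan that already specifies an adjusted primary model would settle the point.

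**Conclusion.** The point holds as a loss of precision, not as an error or contradiction in the plan. Surgical type is pooled, known before allocation, absent from the strata and absent from the stated primary comparison.

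Under the assumed 10–30% revisions and 5–10 dB gap, and with 10 dB as the SD of the mixture, adjustment would remove between 2% and 21% of the variance. At the low end the gain is trivial. At the high end it equals about ten fewer patients needed per group (50 against 40). Since the article supplies neither assumed quantity, the true place within that range, or below it, is unknown. What justifies acting is that the remedy uses a fact already known for every patient and costs almost nothing.

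**What to change.** Replace the unadjusted primary comparison with a prespecified linear model of postoperative air conduction, with treatment group, surgical type (primary versus revision) and the age stratum as terms. Base the equivalence confidence interval on the adjusted difference. Fix this before outcome data are compared between groups, apply the same model to each multiply imputed data set, and keep the unadjusted difference as a supporting result. State also whether the SD of 10 dB refers to the mixed population.

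The cost is one added analysis term for surgical type, the age stratum as a second, and a documented amendment. No extra data are needed, and nothing in patient care changes.

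Adding surgical type as a two-level stratum for patients still to be enrolled is optional. The randomisation chart was set before the start and recruitment is under way. Revisions at 10–30% of 112 would number only about 11 to 34 patients, to be divided further by age. Incomplete blocks in such small cells could undo the balance sought, and the model term delivers most of the benefit without that risk.

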#### Primary outcome measure

Our primary outcome is the postoperative air conduction at approximately two and twelve months postoperatively, as measured by pure-tone audiometry for the following frequencies: 500, 1000, 2000 and 4000 Hz, in accordance with the Committee on Hearing and Equilibrium guidelines for the evaluation of results of treatment of conductive hearing loss [25]. However, thresholds at 3000 Hz were substituted in all cases with those at 4000 Hz, because the 3000 Hz frequency is not part of the standard measurement protocol in the Netherlands.

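### The reason given for an unblinded trial does not reach the person who measures the primary outcome; the audiometry testers could be masked from now on

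*Protocol article*

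**What the plan says.** The Study design section states: "The study design will be a single-center, unblinded, randomized controlled trial". The Abstract describes the trial the same way. The section on randomization, blinding and treatment allocation gives the only justification: "Blinding of both participants and care providers is not possible", since both know where surgery took place and whether the patient stayed. The same section says that the "treatment allocation sequence is concealed for participants, care providers and researchers".

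The primary outcome is "postoperative air conduction at approximately two and twelve months postoperatively, as measured by pure-tone audiometry" (Primary outcome measure). The sample size section sets the aim: "To establish equivalence in postoperative mean air conduction of 5 dB (standard deviation 10" dB), with alpha 0.05, 80% power and 51 participants per group. The Statistical analysis section plans 95% confidence intervals for between-group differences. No section says who performs the audiometry, whether that person knows the arm, or that masking that person is impossible.

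**The concern.** Three roles matter for blinding here: the patient, the care provider and the person who measures the outcome. The article rules out blinding for the first two and then labels the whole trial unblinded. For the third role the label has no reason behind it.

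This is more than a detail left out of a condensed article. The article has a section on blinding and states a choice there. Masking of testers must also be in place when the thresholds are measured, so an analysis plan cannot add it later.

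At stake is the between-group difference in the primary endpoint. If testers know the arm and handle the two arms differently, the difference shifts. In a superiority trial a shift towards zero works against the trial's claim. In an equivalence trial it works in the claim's favour.

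**Working it through.** **1. Does anything else in the article mask the tester?**
- Sequence concealment protects enrolment. It ends once the patient is allocated and does not govern what a tester knows two months later.
- Analysis under a patient identification number (Safety reporting, ethics and funding) protects identity at the analysis stage, not the threshold measurement.

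Neither fills the gap.

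**2. Would the arm be visible at audiometry?** The Intervention section gives both arms stapedotomy under general anesthesia and the same early aftercare: "The ear tampon will be removed in the outpatient clinic seven to ten days postoperatively in both groups". The arms differ in whether the patient stayed the night after surgery. Nothing described at two or twelve months shows this, unless the patient or the paperwork discloses it.

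**3. The plan's own figure.** Inputs from the sample size section: margin 5 dB, SD 10, alpha 0.05, power 80%. Taking alpha as one-sided:

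n = 2 × [10 × (1.645 + 0.842) / 5]² ≈ 49.5, so 50 per group. The t-test version gives 51, as stated.

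**4. Illustration of a differential shift.** Assumptions not in the article: equivalence is declared when the whole confidence interval lies within ±5 dB; the true difference is exactly 5 dB; the tester's shift is b dB towards zero.

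SE = 10 × √(2/51) = 1.980. Equivalence is declared when the observed difference lies within ±(5 − z × SE):
- 90% interval (z = 1.645): ±1.743
- 95% interval (z = 1.960): ±1.119

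P(false equivalence) = Φ[(limit − (5 − b)) / SE] − Φ[(−limit − (5 − b)) / SE]

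For b = 1 with the 90% interval: Φ(−1.140) − Φ(−2.900) = 0.127 − 0.002 = 0.125.

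| Assumed shift towards zero | 90% interval | 95% interval |
|---|---|---|
| 0 dB | 5.0% | 2.4% |
| 1 dB | 12.5% | 6.8% |
| 2 dB | 25.4% | 15.2% |

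**5. The opposite direction.** If the true difference is 0 and the tester introduces a spurious difference, the chance of showing equivalence falls:

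| Spurious difference | 90% interval | 95% interval |
|---|---|---|
| 0 dB | 62.1% | 42.8% |
| 1 dB | 56.3% | 38.2% |
| 2 dB | 41.9% | 27.1% |

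That the 0 dB row lies below 80% is a separate question about the sample size and plays no part in this point.

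**The case against.** The strongest reply is that the mechanism is uncertain. A reader might infer that a tester who expects equal hearing in both arms will shrink a real difference. That does not follow: such an expectation is the same for every patient, does not depend on knowing the arm, and would not be removed by masking. Bias in the difference needs a tester who knows the arm and treats the arms differently. The article does not suggest in which direction, or that it happens at all. This part of the reply stands, and the point is limited accordingly.

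Second, the article does not say who tests or what they are told. The approved protocol, which the article says is in the trial register, may say more. So it cannot be asserted that testers know the arm. What remains is that the article says unblinded without exception and gives a reason that stops short of the assessor.

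Third, pure-tone thresholds rest on the responses of a patient who cannot be masked. This also stands: masking the tester deals with one route of bias only.

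Fourth, the shifts of 1 and 2 dB have no source in the article. They move a whole group mean, and the first table places the true difference exactly on the margin. The figures show how sensitive a 5 dB margin is; they do not estimate the bias.

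**Conclusion.** The point holds in a limited form. The stated reason for an unblinded trial does not cover the measurement of the primary outcome, and the article describes no obstacle to masking it. If testers know the arm, the primary difference could be biased in either direction by an unknown amount. Under the assumptions shown, a shift of 1 to 2 dB towards zero would raise false equivalence from 5.0% to 12.5–25.4% with a 90% interval, or from 2.4% to 6.8–15.2% with the planned 95% interval. A spurious difference of that size where none exists would instead lower the chance of showing equivalence.

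A reader might go further and conclude that the result will be biased towards equivalence, or that masking would make the endpoint free of assessment bias. The article supports neither. This is an inexpensive improvement to the conduct of the trial, not a demonstrated error in its result.

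**What to change.** From now on, mask the people who perform the two- and twelve-month audiometry to allocation: leave the arm off the test request, ask patients not to mention their hospital stay to the tester, and record any unmasking. In the article and the trial report, extend the blinding statement to the testers, and report which audiometry was masked and which was not. Do not label the whole trial assessor-masked: the Trial status section says recruitment is under way, so some tests may already have been done unmasked. If testers are in fact masked already, the only change needed is to correct the word unblinded.

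The cost is a change to the request form, an instruction to patients and a short log. That this is small is a judgement, since the article does not discuss cost. Sample size, endpoint and care are unchanged. The downside is that some patients will reveal their arm, tests already done stay unmasked, and patients' own responses remain unblinded.
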